### Participant Timeline

During the study, participants undergo ocular examinations at baseline and 10 minutes after the intervention. The study procedures for participant recruitment, intervention, assessment, and data follow-up follow the SPIRIT (Standard Protocol Items: Recommendations for Interventional Trials) guidelines (Table 1) [28]. The study process is illustrated in Figure 1.

**Table 1 table1:** Study procedures conducted in accordance with the SPIRIT (Standard Protocol Items: Recommendations for Interventional Trials) guidelines.

Time point			Study period						
			Enrollment		Allocation		After allocation		
			Recruitment (2-4 wk)		Random assignment (0 d)		Baseline		Follow-up
**Enrollment**									
	Eligibility screening	✓							
	Informed consent	✓							
	Random assignment			✓					
**Intervention**									
	Digital ocular massage group					✓		✓	
	EyePeace ocular massage group					✓		✓	
	No ocular massage group					✓		✓	
**Assessments**									
	Intraocular pressure (mm Hg)					✓		✓	
	Best corrected visual acuity (logarithm of the minimum angle of resolution)					✓		✓	
	Schlemm canal area (μm^2^)					✓		✓	
	Schlemm canal diameter (μm)					✓		✓	
	Trabecular meshwork width (μm)					✓		✓	
	Trabecular meshwork thickness (μm)					✓		✓	
	Quality of Vision Questionnaire score					✓		✓	

**Figure 1 figure1:**
[figure not shown]
Study design flowchart. AE: adverse event; IOP: intraocular pressure; QoV: Quality of Vision; SC: Schlemm canal; TM: trabecular meshwork; TMUEH: Tianjin Medical University Eye Hospital.

### Sample Size

On the basis of the stated assumptions (a common SD of 1.9 and a maximum mean difference in IOP between groups of approximately 2 mmHg), a total of 36 participants (72 eyes [participants will contribute both eyes unless exclusion criteria apply]; 3 groups; 24 eyes per group) are required to achieve 90% power at α=.05 [1,5]. This corresponds to 3 groups of equal size in a randomized controlled trial. The calculations use a 1-way analysis of variance to test overall mean differences and consider a moderate to large effect size in IOP reduction. Allowing for a 10% dropout rate, the recruitment target is 40 participants (80 eyes). If further data refine the expected mean difference, the sample size will be adjusted accordingly (larger samples for smaller expected differences and vice versa).

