## Methods

### Study Design

This single-masked, randomized controlled trial will enroll 36 healthy Chinese participants (72 eyes) aged 18 years or older. They will be randomly assigned in a 1:1:1 ratio to the digital ocular massage group (24 eyes), EyePeace ocular massage group (24 eyes), or no ocular massage (24 eyes). The trial will be conducted at Tianjin Medical University Eye Hospital (TMUEH) in Tianjin, China, a nationally accredited clinical trial site. Healthy participants who voluntarily consent to undergo ocular massage will be invited to join this study to assess noninvasive clinical parameters. Patients and the public will not be involved in the design, implementation, reporting, or dissemination of this study. This study was registered on the Chinese Clinical Trial Registry (ChiCTR2400093512) on December 6, 2024.

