### Statistical Methods

Following the guidelines for statistical analysis plans in clinical trials [18,29], all statistical analyses will be conducted using SPSS software (version 25.0; IBM Corp). The significance level is set at 5% (2-tailed), with a 95% CI. The normality of data distribution will be assessed using the Shapiro-Wilk test. Data will be compared using 2-way repeated measures analysis of variance. If the hypothesis is unmet (*P*>.05), the Greenhouse-Geisser correction will be applied. Multiple comparisons will be made between groups at different time points using the Bonferroni-Holm correction. If the Shapiro-Wilk test indicates that the data are not normally distributed (*P*<.05), nonparametric tests will be used: paired comparisons will use the Wilcoxon signed-rank test, and between-group comparisons will use the Kruskal-Wallis H test. Statistical significance will be considered at *P*<.05 for 2-tailed tests unless otherwise specified. To ensure participant safety, the distribution of AEs will be described for both digital ocular massage and EyePeace ocular massage groups. The incidence rates of AEs were compared using the chi-square test or the Fisher exact test, as appropriate. An intention-to-treat analysis will be the primary analytic approach. All participants will be included in the analysis based on their original allocation, regardless of protocol adherence. For missing data, multiple imputation will be performed using the fully conditional specification method, assuming data are missing at random. A sensitivity analysis using a per-protocol approach will also be conducted to compare results. Given the short duration of this study, an interim analysis will not be performed.

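### Sample size and planned tests count the two eyes of one participant as independent, so 90% power is not delivered and an eye-level primary test rejects too often

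*Protocol article*

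**What the plan says.** The Study Design section says the trial "will enroll 36 healthy Chinese participants (72 eyes) aged 18 years or older" and gives each of the three arms as 24 eyes. The Interventions and Allocation sections randomise participants, not eyes, so both eyes of a person fall in the same arm.

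The Sample Size section assumes "a common SD of 1.9 and a maximum mean difference in IOP between groups of approximately 2 mmHg" and concludes that "24 eyes per group) are required to achieve 90% power", with α set at 0.05. On method it says: "The calculations use a 1-way analysis of variance to test overall mean differences". It counts "72 eyes [participants will contribute both eyes unless exclusion criteria apply". No inter-eye correlation or design effect is given.

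The Statistical Methods section says: "Data will be compared using 2-way repeated measures analysis of variance". If normality fails, it falls back on the Wilcoxon signed-rank and Kruskal-Wallis tests. It does not mention averaging the eyes, selecting one eye, a mixed model or any other allowance for two eyes per person.

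**The concern.** Two eyes of one person share anatomy, measurement session and, here, treatment, so they should not be assumed to give independent readings. When whole people are randomised, the second eye adds less information than a new participant would. An analysis that counts eyes as independent then has two faults. The sample size is too optimistic. The standard errors are too small, so confidence intervals are too narrow and the false-positive rate exceeds 5%. Both bear on the primary IOP comparison, and the second would reach the eye-level secondary outcomes too (visual acuity, Schlemm canal and trabecular meshwork measures).

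**Working it through.** **Inputs.** From Sample Size: SD 1.9, largest difference between group means 2 mm Hg, α 0.05, power 90%, three groups, one-way ANOVA, 24 eyes per group. From Study Design and Sample Size: 36 participants, hence 36/3 = 12 per group with two eyes each. Not in the protocol: the correlation between fellow eyes (ICC), assumed here to lie between 0.3 and 0.9, and the position of the third mean.

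**Step 1: reproduce the stated figure.** Put the third arm midway, with means −1, 0, +1.

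- Effect size: f = √[(1 + 0 + 1)/3] / 1.9 = 0.430.
- Noncentrality: λ = n × Σ(mean − grand mean)² / SD² = 24 × 2 / 3.61 = 13.30, with 2 and 69 degrees of freedom.
- Power from the noncentral F distribution: 0.902 at 24 per group and 0.888 at 23 per group.

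So 24 is the smallest group size that reaches 90%, which matches the protocol exactly. The match requires 72 independent observations. With means 0, 0, 2 the same method needs only 19 per group, so the midway pattern is the one that explains the stated number.

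**Step 2: power with the participant as the unit.** The mean of two eyes has SD 1.9 × √[(1 + ICC)/2]. With 12 participants per group the F test has 2 and 33 degrees of freedom. For example, at ICC 0.5 the SD is 1.9 × √0.75 = 1.645, λ = 12 × 2 / 2.707 = 8.86, and power is 0.72.

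| Assumed ICC | Power, means −1, 0, +1 | Power, means 0, 0, 2 | Participants for 90% (means −1, 0, +1), before / after 10% dropout |
|---|---|---|---|
| 0.3 | 0.79 | 0.89 | 48 / 54 |
| 0.5 | 0.72 | 0.85 | 57 / 64 |
| 0.7 | 0.66 | 0.79 | 63 / 70 |
| 0.8 | 0.64 | 0.77 | 66 / 74 |
| 0.9 | 0.61 | 0.75 | 69 / 77 |

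In terms of information, 72 eyes are worth 72/(1 + ICC) independent ones: 48 at ICC 0.5 and about 38 at ICC 0.9. Under the midway pattern, power is 0.886 even at ICC 0, because the denominator degrees of freedom fall from 69 to 33.

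**Step 3: false-positive rate of an eye-level test.** With two time points, the group-by-time test in a repeated measures ANOVA is a one-way ANOVA on change. A one-way F test on 24 eyes per group, generated as 12 correlated pairs with no true difference, was simulated 200,000 times per ICC.

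| Assumed ICC | Rejection rate at nominal 5% |
|---|---|
| 0 | 0.049 |
| 0.3 | 0.10 |
| 0.5 | 0.14 |
| 0.7 | 0.18 |
| 0.8 | 0.20 |
| 0.9 | 0.22 |

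Under the midway alternative, this invalid test still rejects in only 0.88 (ICC 0.3) to 0.86 (ICC 0.9) of simulated trials.

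**Step 4: the number actually recruited.** The Results section reports 50 participants, or 16 to 17 per arm. The Step 2 formula with n = 16 and 17 and the midway pattern gives power 0.90 to 0.92 at ICC 0.3 and 0.78 to 0.81 at ICC 0.8.

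**The case against.** The strongest objection is that the Statistical Methods never name the unit of analysis, and a fuller analysis plan might handle the pairing of eyes. This stands in part: the false-positive rates in Step 3 apply only if the ANOVA is run on eyes without a participant term. But every group size is stated in eyes, and neither the named ANOVA nor its nonparametric fallback accommodates two eyes within a person, so eye-level analysis is the natural reading. A clustered analysis would control the error rate, but the 90% power would still be wrong.

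Second, the size of the shortfall depends on assumptions. With means 0, 0, 2 and ICC 0.3, power is 0.89, about one point short. The relevant ICC is that of the quantity analysed, which may be change in IOP rather than IOP itself, and it could be below 0.3: at ICC 0.1 the midway pattern gives 0.85. This is fair, and is why a range is shown.

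Third, 50 participants were recruited rather than 36. That recovers much of the power: with means 0, 0, 2 it is at least 0.97 at ICC 0.3 and about 0.89 to 0.91 at ICC 0.8. It does nothing for the error rate of an eye-level test.

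Finally, nothing says that questionnaire scores or adverse events would be duplicated by eye. That risk arises only if everything is held in one eye-level data set, and the conclusion does not rest on it.

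**Conclusion.** The concern holds. The stated 90% power comes from treating 72 eyes of 36 participants as 72 independent units. Under the pattern of means that reproduces the protocol's own figure, a valid test has about 61% to 79% power for inter-eye correlations of 0.9 to 0.3. Under the more favourable pattern it has 75% to 89%, still below the claim. If the planned ANOVA is run on eyes, as the document reads, its true false-positive rate is about 10% to 22% over the same range. The power conclusion follows from the protocol's own inputs once fellow eyes are recognised as clustered. Its exact size depends on the assumed correlation and pattern of means. The error-rate conclusion depends further on eye-level analysis.

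**What to change.** State in the Statistical Methods that the participant is the unit of inference. Either of these would do for IOP, visual acuity, Schlemm canal and trabecular meshwork outcomes:

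- analyse one value per participant, the mean of the two eyes where both are eligible; or
- fit an eye-level linear mixed model to change, or to the post-intervention value adjusted for baseline, with a random participant intercept.

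If both time points stay in one repeated measures model, a participant intercept alone is not enough, because it cancels out of the change. A participant-by-time term is needed as well. Any nonparametric fallback should use one value per participant. Questionnaire items and adverse events should be analysed once per participant.

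Restate the Sample Size section with its assumptions declared. For example: 36 participants (12 per group) give about 61% to 79% power for a 2 mm Hg maximum difference with the third group midway, for inter-eye correlations of 0.9 to 0.3. Add the corresponding figure for the 50 recruited, and report the observed inter-eye correlation with the results.

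The cost is a change of analysis wording and a less favourable stated power. No new participants or measurements are needed. Data collection is complete, so the change should be recorded before the masked analysts see results by group.

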### Recruitment

This study will be conducted from March to June 2025 at TMUEH. Healthy participants in Tianjin, China, will be invited to participate. Recruitment will be carried out through posters, online advertisements, and social media platforms. Specialized professionals will collect demographic information of the participants during the initial screening.

### Allocation

The patients will be randomly assigned to 1 of 3 groups: digital ocular massage (group A), EyePeace ocular massage (group B), or no ocular massage (group C). Randomization will be performed by a statistician using a network-based randomization procedure with a fixed block size of 4 to ensure balanced group allocation. Group assignments will be placed in sealed, opaque envelopes held by the PI. Each envelope will include the participant’s information and intervention assignment.

This trial will use a single-masked design. Participants will be aware of their assigned intervention (digital ocular massage, EyePeace ocular massage, or no ocular massage). However, the data analysis team and clinical assessment staff will remain masked to group allocation. All clinical assessments will be performed by a masked examiner who is not involved in data collection or group allocation. The conditions and protocols for disclosure of group information, if required, will be established and overseen by the PI.

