### Interventions

Eligible participants will be randomly assigned in a 1:1:1 ratio to (1) digital ocular massage (group A), (2) EyePeace ocular massage (group B), or (3) no ocular massage (group C). Group A and group B participants will receive ocular massage for 10 minutes [5,10,11]. Any participant experiencing an adverse event (AE) will be withdrawn from the trial, documented, provided appropriate treatment, and referred immediately to the principal investigator (PI). Clinical research staff will receive professional training covering participant enrollment, treatment procedures (including risks and benefits), and data collection processes. Participants will be sufficiently informed about the study and provided with compliance education to enhance participation and minimize noncompliance. Study staff will proactively contact participants in advance by telephone or SMS text message. EyePeace is a flexible, medical-grade silicone device designed to apply gentle, pulsatile vertical pressure to the closed eyelids. Although it does not contain a built-in pressure gauge, manufacturer specifications suggest that the applied force typically ranges from 0.2 to 0.5 N. To ensure consistency, all participants in the EyePeace ocular massage group received standardized instructions and a demonstration before use. In addition, a trained examiner supervised the massage procedure to ensure correct technique and duration. For the digital ocular massage group, clinical staff applied consistent fingertip pressure guided by prior training and feedback from pilot sessions, aiming to replicate the mechanical effect of the EyePeace ocular massage device. Although exact biomechanical equivalence between digital ocular massage and EyePeace ocular massage cannot be assured, the standardization procedures were designed to ensure comparability in massage duration, eyelid area coverage, and application frequency.

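### A fixed block of 4 cannot be balanced over three arms, so the stated randomization does not ensure the 1:1:1 allocation that it is meant to secure

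*Protocol article*

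**What the plan says.** The protocol article fixes the ratio in two places. Study Design has participants "randomly assigned in a 1:1:1 ratio to the digital ocular massage group (24 eyes") and likewise 24 eyes in each of the other two arms. Interventions repeats it: "Eligible participants will be randomly assigned in a 1:1:1 ratio to (1) digital ocular massage (group A").

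The unit randomized is the person, not the eye; Allocation has "The patients will be randomly assigned to 1 of 3 groups". Sample Size then rests on three equal groups: "participants will contribute both eyes unless exclusion criteria apply]; 3 groups; 24 eyes per group) are required to achieve 90% power at α=.05". With both eyes contributing, that is 12 participants per arm. The section inflates 36 participants to a recruitment target of 40 for 10% dropout.

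The means of reaching these equal groups is given once, in Allocation: "using a network-based randomization procedure with a fixed block size of 4 to ensure balanced group allocation". The article describes no unequal or rotating block composition, no second block size and no other balancing device.

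**The concern.** Blocking balances the arms because each completed block holds every arm in the intended ratio. For three equally weighted arms, the block size must be a multiple of three. A block of 4 must give one arm an extra place, so the stated purpose of the block size does not follow from the stated block size.

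Either the sentence misreports what was done, or the list was not built from 1:1:1 blocks. In both cases a reader cannot reproduce or audit the randomization, on which every between-group comparison rests. It is also unclear whether the arms reached the planned 24 eyes each.

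Predictability is a lesser matter. The block is small and fixed, and the arms are openly known ("Participants will be aware of their assigned intervention"), so someone who knew the block size and the past assignments could sometimes deduce the last place in a block.

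**Working it through.** **Inputs.** Three arms, 1:1:1 (Study Design, Interventions). Block size 4, fixed (Allocation). 36 participants, 72 eyes, 24 eyes per group, 90% power, α = 0.05; "a common SD of 1.9 and a maximum mean difference in IOP between groups of approximately 2 mmHg"; one-way analysis of variance (all Sample Size). Not in the article and assumed here: each block of 4 is filled 2:1:1.

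**1. The plan's own figure.** Take group means 0, 1, 2 and SD 1.9.
- Effect size f = √(2/3)/1.9 = 0.43.
- Noncentrality with 24 per group: λ = 24 × (1 + 0 + 1)/1.9² = 48/3.61 = 13.30, on 2 and 69 degrees of freedom.
- Power = 0.902, and 24 is the smallest group size reaching 90%.
- Dropout: 36/0.9 = 40.

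The stated sample size therefore reproduces, for equal groups and with eyes counted as independent.

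**2. Divisibility.** 4 = 3 × 1 + 1. One place is left over in every block, so the nearest composition to 1:1:1 is 2:1:1. 36/4 = 9 complete blocks, so each arm gets 9 places plus however many of the 9 extra places fall to it.

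**3. Where the extra places go.**
- *Doubled arm rotated evenly:* 3 extras each, giving exactly 12/12/12.
- *Doubled arm drawn at random in each block:* the extras are multinomial with 3⁹ = 19683 equally likely sequences.
  - 12/12/12: 9!/(3!3!3!) = 1680, and 1680/19683 = 8.5%.
  - 13/12/11 in any order: 6 × 9!/(4!3!2!) = 6 × 1260 = 7560, which is 38.4%.
  - A largest-to-smallest gap of 1 is impossible, because the extras sum to 9. A gap of 3 or more is therefore 19683 − 1680 − 7560 = 10443, which is 53.1%.
- *Same arm always doubled:* 18/9/9, or 36/18/18 eyes.

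**4. Effect on power.** Means 0, 1, 2 are kept, with λ = Σnᵢ(mᵢ − m̄)²/3.61, where m̄ is the weighted mean. Eyes are listed in the order of the means.

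| Eyes per arm | Σnᵢ(mᵢ − m̄)² | λ | Power |
|---|---|---|---|
| 24/24/24 | 48.00 | 13.30 | 0.902 |
| 26/24/22 | 47.78 | 13.23 | 0.900 |
| 28/24/20 | 47.11 | 13.05 | 0.896 |
| 22/28/22 | 44.00 | 12.19 | 0.874 |
| 36/18/18 | 49.50 | 13.71 | 0.911 |
| 18/36/18 | 36.00 | 9.97 | 0.796 |

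An oversized arm costs power when it is the one with the middle mean. Averaged over all random-doubling lists with the weights of step 3, power is 0.898.

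**5. What block size fits.** Blocks of 3, 6, 9 or 12 divide 36 into 12, 6, 4 or 3 whole blocks and give exactly 12 participants per arm. The target of 40 is not a multiple of 3, so it cannot split equally under any block size (nearest 13/13/14).

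**The case against.** A reader might infer that 24 eyes per group is unattainable under this procedure. The document does not support that. Nine blocks of 4 end at 12/12/12 if the doubled arm is rotated, and can do so by chance. The procedure fails to ensure balance; it does not rule it out.

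A reader might also infer that the trial loses its power. That does not follow either. Modest imbalance costs a few percentage points at most, and nothing in the article says that one arm is always doubled.

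The 2:1:1 composition is itself an assumption. The sentence may simply misstate the block size, and then the imbalance figures do not apply. Results reports 50 recruited by July 15, 2025. If all were randomized, which is not stated, 12 complete blocks (48 people) would put at least 12 in every arm before dropout, even at 24/12/12.

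On concealment, Allocation specifies a list made by a statistician, sealed opaque envelopes and masked assessors, and does not say that enrolling staff know the block size. Nor is 4 worse than a fixed block of 3, where the third place is always determined. In a randomly doubled 2:1:1 block, the fourth place is determined only when the first three contain a repeat: 6 of the 12 orderings, or half.

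All of this stands, and it limits the consequence. It does not remove the contradiction, because no fuller document can make 4 divisible by 3.

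**Conclusion.** The point holds as an internal contradiction. The block size in Allocation is incompatible with the three equal groups in Study Design, Interventions and Sample Size, so balance is claimed but not ensured.

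Its size depends on a composition the article does not give. With random 2:1:1 blocks and 36 participants, exact balance occurs in 8.5% of lists and a gap of 3 or more participants in 53%, while average power stays near the planned 0.90. Only constant doubling with the middle-mean arm enlarged would bring power down to about 0.80. These power figures take the plan's SD and difference, evenly spaced means and independent eyes.

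The main harm is a randomization that is either misreported or not the one described, rather than lost power. Predictability of a small fixed block is secondary.

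**What to change.** The Abstract reports data collection completed in summer 2025, so allocation appears to be finished and a new list is probably moot. In Allocation, state the randomization procedure and block size actually used, including how each block was filled, and replace the present sentence. Report the number of participants and of eyes allocated to each arm. If blocks of 4 were really used, say so and drop the claim that they ensured balance.

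If any allocation remains, use permuted blocks whose sizes are multiples of 3, for example 3 and 6 in random order, not disclosed to enrolling staff. For totals such as 40 that are not multiples of 3, do not promise exact equality.

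The cost is a corrected sentence and a line of counts. It needs no further participants or measurements.
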